### Data analysis

Analysis of covariance (ANCOVA) will be used to examine CA and PA at follow up, co-varying for baseline levels. Two contrasts will be examined: a comparison between Group 1 and Groups 2 and 3 combined, addressing the question of whether goal-setting is effective in increasing CA and PA, and a comparison between Group 2 and Group 3, addressing the question of whether goal-setting supplemented with mentoring is more effective than goal-setting alone. The results will provide information about effect sizes and variability of response which will be needed for the design of a definitive trial. Data from the secondary outcome measures will be examined to inform the selection of measures for a definitive trial. QRISK2 scores will be compared to examine whether they provide confirmatory evidence of behavior change. Health economic analyses will be conducted to inform modeling for the definitive trial: primary cost-utility analysis; secondary cost-consequence analysis; cost-effectiveness acceptability curve. Background data and process measures will be examined to inform our understanding of the likely sample characteristics which would be encountered in a definitive trial, allowing us to consider variables that may have important influences on outcome or on the process of participation and prepare a comprehensive analysis plan.

Qualitative interview data, analyzed using a biographical narrative method, will contribute a deeper understanding of participants’ expectations and reasons for participating, the meanings they attach to health-related behavior, and the processes within which they actively engage (or not) with the challenges of aging [38]. These data will help to further develop and refine the intervention.

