### Participants

All individuals aged over 50 years living in the local community and attending the community resource center will be invited to participate, with no exclusions. If they do not wish to take part in research they may still attend the center, and in this case only records of attendance and activity participation will be taken. Sample size calculation for this feasibility study is based on anticipated attendance rates. We expect to randomize at least 75 individuals (target *n* = 25 per condition). Reasons for declining to participate will be recorded where given, although participants are not required to give this information. Attrition at any stage will be noted and reasons recorded where available, although participants are free to withdraw without giving a reason.

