Those center attendees willing to participate in the RCT will be randomly allocated using a sequentially-randomized dynamic adaptive computer algorithm developed by the trials unit (NWORTH) and incorporating stratification by gender to one of three conditions following initial assessment [13]. Each condition involves a one-to-one interview with an appropriately-trained professional, lasting up to 1.5 h, as follows:

1. Group 1, control, will have a general discussion about the facilities and activities available.

2. Group 2, goal-setting, will have a structured goal-setting interview using the Bangor Goal-Setting Interview. The interview will explore current functioning in relation to PA and CA, as well as considering social engagement, diet, and health. The interviewer will have access to key information from the initial assessment such as details of identified health risks. Areas where the participant would like to make changes or improvements will be identified and prioritized, and up to five specific, realistic and achievable goals will be identified. Examples of goals might be increasing walking to 30 min per day, or learning to use email to communicate with a friend. Current performance, satisfaction with performance, and degree of confidence in carrying out the activity, will be rated by the participant on a scale of 1 to 10. Behavioral indicators of partial (25%, 50%, 75%) and complete goal attainment will be established for each goal. Ways in which the goal may be addressed will be discussed and linked to center activities (for example, walking group, computer skills sessions) or external facilities (such as, GP consultation, smoking cessation group), and a written individual action plan will be prepared.

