The study will allow us to establish a demographic profile of participants and provide an understanding of who attends the Centre and why. It will also allow us to examine the extent to which the approach taken in the study is acceptable to people attending the Centre. While Centre attenders do not have to give a reason for either declining participation or withdrawing from the study, every effort will be made to obtain feedback on reasons for making such decisions. We anticipate that there will be more female than male attendees and randomization has been stratified to take account of gender. It will also be valuable to identify the age profile of attenders and if appropriate age will be taken into account in the statistical analysis.

The study findings will contribute to establishing an effective approach to promoting mental and physical health, enhancing mobility and independence, improving well-being and QoL, and identifying an effective means of preventing, delaying, or reducing the impact of, age-related disability and disease. The research integrates psychological, social, physiological, medical, epidemiological, public health, and economic perspectives, making it possible to consider the complex interactions between factors operating at each of these levels to determine health and wellbeing in later life.

This feasibility study contributes to establishing the effectiveness of lifestyle interventions in promoting healthy aging, preventing or delaying the onset of disability, and reducing costs of health and social care. Current knowledge is at a stage where we can begin to develop interventions addressing these aims [4], and this study will provide much-needed evidence to inform policy and support the development of approaches that can eventually produce benefits at population level.

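### Randomisation is stratified by gender, but the stated primary ANCOVA names only the baseline score as covariate; adding gender is a nearly free improvement, and the role of age should be fixed before follow-up data are seen

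*Protocol article*

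**What the plan says.** The Intervention section of the protocol article allocates consenting attendees by an adaptive computer algorithm "incorporating stratification by gender to one of three conditions following initial assessment". Gender is the only stratification factor named. The Discussion repeats this: "We anticipate that there will be more female than male attendees and randomization has been stratified to take account of gender".

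The Data analysis section gives the primary model in one sentence: "Analysis of covariance (ANCOVA) will be used to examine CA and PA at follow up, co-varying for baseline levels". Two contrasts follow: "a comparison between Group 1 and Groups 2 and 3 combined", and "a comparison between Group 2 and Group 3". Gender is not mentioned in that section. The same section says that the effect sizes and variability found here will feed the design of a definitive trial.

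On age, the Discussion says that the age profile of attenders will be identified and that "if appropriate age will be taken into account in the statistical analysis". It gives no criterion for what is appropriate and no time for the decision.

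On size, the Participants section says: "We expect to randomize at least 75 individuals", with a target of 25 per condition. It adds: "Sample size calculation for this feasibility study is based on anticipated attendance rates".

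**The concern.** Stratifying by gender brings the arms close to the same gender mix. A gender difference in the outcome then adds little or nothing to the chance variation of an arm difference. A model without gender still counts that difference as residual noise, so the reported standard error is larger than the true variability of the estimate. Intervals come out too wide and the tests reject too rarely. In a feasibility study the residual SD matters as much as the tests, because it is one of the quantities carried forward to size the next trial.

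The age wording raises a separate question. With no criterion and no decision time, each primary outcome has two candidate models, and nothing in the text prevents a choice between them after the results are known.

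**Working it through.** **Inputs from the protocol article.** Three arms with a target of 25 each; gender as stratification factor; baseline score as the named covariate; two contrasts.

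**Inputs assumed, because the article gives none.** Partial correlation r between gender and the 12-month score given baseline, 0 to 0.5; 70% women; baseline slope 0.6 with residual SD 1; two-sided alpha 0.05.

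**Step 1: the plan's own figure.** 3 × 25 = 75, as stated. The sample size rests on attendance, so there is no power calculation to reproduce. The stated model has an intercept, two contrasts and one covariate, leaving 75 − 4 = 71 residual degrees of freedom. With gender there are 70.

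**Step 2: standard error with and without gender.** The standard error of a contrast is about residual SD × c. For the first contrast c = √(1/25 + 1/50) = 0.245; for the second c = √(1/25 + 1/25) = 0.283. With gender balanced, c is the same in both models. Adding gender multiplies the residual variance by (1 − r²). Hence

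SE without gender / SE with gender ≈ 1/√(1 − r²).

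Required sample size is proportional to residual variance. Planning an adjusted definitive trial on the unadjusted SD therefore multiplies n by 1/(1 − r²).

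**Step 3: simulation under the null.** 20,000 trials per setting, N = 75, with gender-stratified permuted blocks of three standing in for the adaptive algorithm. Age had the same r as gender in the settings up to 0.3, and 0.3 where gender had 0.5. Monte Carlo error is about √(0.05 × 0.95/20,000) = 0.15 percentage points.

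| r | SE ratio (formula) | multiplier on n | type I error without gender, contrast 1 / 2 |
|---|---|---|---|
| 0 | 1.000 | 1.00 | 5.1% / 4.8% |
| 0.1 | 1.005 | 1.01 | 4.9% / 4.7% |
| 0.2 | 1.021 | 1.04 | 4.7% / 4.5% |
| 0.3 | 1.048 | 1.10 | 4.0% / 3.7% |
| 0.4 | 1.091 | 1.19 | not simulated |
| 0.5 | 1.155 | 1.33 | 2.4% / 2.5% |

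With gender in the model, type I error lay between 4.7% and 5.2% in every setting. At r = 0.3, first contrast, the mean reported standard error without gender was 0.2462, while the estimates varied with SD 0.2349 (ratio 1.048). With gender the figures were 0.2346 and 0.2342. At r = 0 the mean standard errors were 0.2457 without and 0.2459 with gender, so adding a gender term that predicts nothing costs almost nothing.

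**Step 4: optional age.** The worst use of the freedom is to report the smaller of the p-values with and without age (gender omitted from both). When neither age nor gender predicts outcome, type I error rises from 5.1% to 5.6% and from 4.8% to 5.3% for the two contrasts. At r = 0.3 for both variables it reaches 5.2% and 4.8%. The rise there is larger, but it starts from the conservative 4.0% and 3.7%. The highest rate in any setting was 5.6%.

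**The case against.** The strongest objection is scope. This is a journal article, and a full covariate list is often left to a statistical analysis plan, which is not shown. The Data analysis sentence names the baseline score but does not say that nothing else will be included. A reader might infer that gender has been ruled out; the text does not say so. Still, the article states a model for its primary outcomes, and a better one is available at almost no cost, so the suggestion stands whether or not a later document already contains it.

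A reader might also infer that the standard errors are certainly overstated. They are overstated only if gender predicts follow-up beyond the same person's baseline score, and the article has no figure for that. Some PASE items, such as housework, home repairs and caregiving, make a gender difference plausible, but a stable difference is largely carried by the baseline score already in the model. Small values of r are therefore quite possible.

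The simulation also assumes tight balance. With a looser adaptive biased coin (assumed; 3,000 trials, Monte Carlo error about 0.4 points), type I error at r² = 0.10 was about 4.4%, and about 4.5% with 20% random attrition (also assumed). The effect may thus be smaller than in the table, though these figures are too imprecise to say by how much.

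The consequences are limited. The error is conservative, and the study makes no power claim. With 71 degrees of freedom, the 95% interval for an estimated SD runs from about −14% to +20%, well beyond a 5% excess. The SD can also be recomputed with gender from the same data.

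On age, a reader might infer a post-hoc choice. The age profile is baseline information. Recruitment was scheduled from 2 January to 30 September 2012, and outcomes come 12 months after entry, so the first are due about January 2013, after the planned close of recruitment. The decision could be made before any outcome exists. What remains is that the text does not require this.

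**Conclusion.** The point holds as a modest, conditional one. Gender is the stratification factor and is not named in the stated primary ANCOVA. If it predicts 12-month FCAS or PASE given baseline, standard errors and the residual SD are too large by 0 to 2% for r up to 0.2 and about 5% at r = 0.3, and the tests are conservative. At r = 0 there is no effect. An excess near 15% needs r = 0.5, for which the article offers no support. All these sizes rest on assumed correlations and on close gender balance at analysis. Nothing here biases the arm comparisons or invalidates the trial.

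The age wording is a lesser weakness: an open choice worth at most about half a percentage point of type I error above 5% in the settings examined. Age is not a stratification factor, so the argument for gender does not by itself make age adjustment mandatory.

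**What to change.** State the primary model for both FCAS and PASE, and for both contrasts, as 12-month score = arm + baseline score + gender. Report the residual SD from this model as the planning value for a definitive trial that will also adjust for gender. The cost is one sentence and one residual degree of freedom (71 to 70 at full follow-up). Gender is already known, because the randomisation needs it.

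Replace the conditional wording on age with a decision made before any follow-up data are seen: either age is a named covariate in both primary models, or it appears only in a sensitivity analysis. Age is already collected at initial assessment. As a linear covariate it would take one further degree of freedom; as a sensitivity analysis it would leave the primary model unchanged.

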We aim to establish the feasibility of an innovative approach to increasing CA and PA among over-50s, including ‘hard to reach’ groups, based on goal-setting. Setting oneself stimulating but achievable goals is an effective means of changing behavior [9], providing motivation to perform better or maintain effort. The social cognitive theory of health behavior change [10] posits that this is most effective where perceived self-efficacy is such that the individual believes it is possible to achieve the desired effects through his/her own actions, and where adopting different behaviors proves enjoyable and socially-rewarding and enhances self-worth. Behavior change is most likely where the environment supports implementation of the desired behavior [11] through availability of peer support and accessibility of facilities and opportunities that can be matched with personal goals, and provides a means of overcoming perceived obstacles. In line with social cognitive theory, we will examine the benefits of developing a context that provides social and material support for behavior change, and of using a goal-setting intervention, with or without follow-up mentoring aimed at boosting self-efficacy and encouraging problem-solving regarding obstacles to change, to optimize use of this resource compared to simple access to facilities. We hypothesize that goal-setting, especially when accompanied by ongoing mentoring, will optimize engagement, leading to increased CA and PA, with benefits for cognitive, physical, social and psychological functioning, health, and QoL.

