3. Group 3, goal-setting with mentoring, will receive the same interview as Group 2 plus a follow-up mentoring phone call from the interviewer after 1 month (in month 2 of participation in the study) and then bi-monthly thereafter (in months 4, 6, 8, and 10) to review progress, problem-solve regarding any obstacles to progress, encourage and reinforce successes, and support maintenance of change. Each participant will remain in the study for 12 months, and will engage according to personal choice in center and related activities. Attendance and activity participation will be recorded. All participants will be reassessed after 12 months by a researcher blind to group allocation. At follow-up assessment, participants will re-rate performance and satisfaction with regard to each identified goal, and a rating of goal attainment will be made.

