### Procedure

Individuals attending the Centre will be given information about the study and invited to consider participating in the trial by a member of the research team, after which they will be given as much time as they need to decide whether they wish to take part. Those who consent to participate will complete the baseline assessment in two face-to-face sessions with a researcher, one focusing on psychological, social and cognitive measures and lasting approximately 1.5 h, and the other focusing on physical health and fitness and lasting approximately 1 h. The researcher will then trigger the randomization. Participants will be allocated to one of the three conditions and will engage in the interview conducted according to the protocol for their allocated condition. Those in the goal-setting with mentoring group will have bi-monthly mentoring phone calls from the interviewer over the following 12 months while the remainder will have no such contact. After 12 months all participants will engage in a follow-up interview in accordance with the condition to which they were allocated; for participants in the goal-setting and goal-setting with mentoring groups the interviewer will use the Bangor Goal-setting Interview to elicit current ratings of performance and satisfaction with performance for the originally-identified goals, while those in the control group will have a general discussion with the interviewer. The interviewer will then trigger the follow-up assessment and all participants will be reassessed by blinded members of the research team.

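### The contrast said to test goal-setting estimates goal-setting plus half of any mentoring effect, and the comparison that isolates goal-setting is not among the two planned

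*Protocol article*

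**What the plan says.** The Data analysis section specifies an ANCOVA of cognitive activity (CA) and physical activity (PA) at follow-up, adjusted for baseline, and then states: "Two contrasts will be examined". Each contrast is tied to a question:

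- The first is "a comparison between Group 1 and Groups 2 and 3 combined, addressing the question of whether goal-setting is effective in increasing CA and PA".
- The second is "a comparison between Group 2 and Group 3, addressing the question of whether goal-setting supplemented with mentoring is more effective than goal-setting alone".

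The arms are described elsewhere. Under Intervention, Group 3 "will receive the same interview as Group 2 plus a follow-up mentoring phone call from the interviewer after 1 month", with further calls in months 4, 6, 8 and 10. Under Procedure, the mentored group is called over the 12 months "while the remainder will have no such contact".

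The Background section gives the aim as "using a goal-setting intervention, with or without follow-up mentoring aimed at boosting self-efficacy", set against simple access to the facilities. It also states the expected direction: "We hypothesize that goal-setting, especially when accompanied by ongoing mentoring, will optimize engagement".

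On the use of the results, the Data analysis section says: "The results will provide information about effect sizes and variability of response which will be needed for the design of a definitive trial".

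**The concern.** Half of the pooled arm receives a second active component, the mentoring calls, that the control arm does not. The difference between the pooled arm and control is therefore not the effect of the goal-setting interview unless mentoring adds nothing, and the authors expect it to add something. Under their own hypothesis, the first contrast does not estimate what the attached question asks.

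Two things are at stake. The first is interpretation: a positive pooled contrast could be read as evidence for the goal-setting interview when some or all of the benefit came from the calls. The second is planning. The definitive trial would test either goal-setting or goal-setting with mentoring, and if the pooled figure is taken forward, it is an average that matches neither when mentoring has an effect.

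**Working it through.** **Inputs from the article.** There are three arms with a target of 25 each (Participants section), and 3 × 25 = 75, which agrees with the stated total. That total rests on anticipated attendance, so there is no power calculation to reproduce. The model is ANCOVA with the two contrasts above.

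**Inputs assumed, not in the article.** Two-sided 5% test; 25 analysed per arm (no attrition); correlation r between baseline and follow-up of 0.6, with a range of 0.5 to 0.7; a scenario with g = 0 and m = 0.5 SD.

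**Step 1: what the contrasts estimate.** Let g be the Group 2 minus Group 1 difference and m the Group 3 minus Group 2 difference. Relative to Group 1, the expected values are g in Group 2 and g + m in Group 3.

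- Contrast 1 (pooled minus control): [g + (g + m)]/2 = g + m/2.
- Contrast 2 (Group 3 minus Group 2): m.

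This needs no assumption about SD, correlation or significance level, only equal arms. Contrast 1 equals g only if m = 0.

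**Step 2: what can be recovered.** g = contrast 1 − (contrast 2)/2, and g + m = contrast 1 + (contrast 2)/2. The two contrasts together hold all the information, but the article plans neither of these combinations.

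**Step 3: standard errors, in units of the follow-up SD before baseline adjustment.**

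- Pooled, 25 vs 50: √(1/25 + 1/50) = 0.245.
- Pairwise, 25 vs 25: √(2/25) = 0.283.
- Ratio: 0.283/0.245 = 1.155.

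Baseline adjustment multiplies both by √(1 − r²), which is 0.8 at r = 0.6. They become 0.196 and 0.226, and the ratio is unchanged.

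**Step 4: size under the assumed scenario (g = 0, m = 0.5 SD).** Contrast 1 has expectation 0.5/2 = 0.25 SD. At r = 0.6 its non-centrality is 0.25/0.196 = 1.28, and that of contrast 2 is 0.5/0.226 = 2.21. With the residual degrees of freedom of the ANCOVA, 75 − 4 = 71, the non-central t distribution gives the middle two columns. Simulation gives the last.

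| r | Contrast 1 significantly positive | Contrast 2 significant | Contrast 1 significant, contrast 2 not |
|---|---|---|---|
| 0.5 | 21% | 52% | 10% |
| 0.6 | 24% | 59% | 10% |
| 0.7 | 29% | 69% | 9% |

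A direct test of Group 2 versus Group 1 would be significantly positive in 2.5% of trials, because g = 0. At r = 0.6 the 24% splits into about 14% in which contrast 2 is also significant and so points to mentoring, and about 10% in which it is not.

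**The case against.** The strongest reply is that these are two standard orthogonal contrasts. The pooled one matches the Background's aim of examining goal-setting with or without mentoring, and Group 3 does receive the goal-setting interview. The calls follow up goals already set, so a benefit confined to Group 3 would still come from a goal-setting programme. The second contrast estimates the mentoring effect openly. Pooling also gains precision in a 75-person feasibility study that promises only initial evidence.

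Much of this stands, and it rules out several stronger readings that a reader might infer:

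- **That a pure mentoring effect would be reported in full as a goal-setting effect.** Only half of it enters the pooled contrast, and no arm receives mentoring without goals.
- **That the pooled contrast is invalid, or supports no statement about goal-setting.** It is a valid test of goal-setting with or without mentoring.
- **That the plan would declare goal-setting alone effective.** The Data analysis section uses that term only for Group 2 in the second contrast, and it states no decision rule.
- **That a false conclusion follows in 24% of trials.** In more than half of those, the planned second contrast is also significant and shows where the benefit lies.

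What does not fall away is the question attached to the first contrast, which asks about goal-setting without the qualifier. Nothing in the article makes the reading of the first contrast depend on the second, and the second is an imperfect safeguard: in the assumed scenario it misses the mentoring effect in about 41% of trials (100% − 59%). Nor is this detail left to an analysis plan that is not shown, since the article itself fixes the two contrasts and says what each addresses.

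**Conclusion.** The point holds in a limited form. At equal arm sizes the first contrast estimates g + m/2. It answers whether goal-setting with or without mentoring beats the control interview, not whether goal-setting itself is effective. The comparison that would isolate goal-setting is not one of the two planned, and the plan's own hypothesis is that m is above zero.

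The algebra is exact for equal arms. The probabilities are illustrative: about 24% for a significantly positive pooled contrast when goal-setting alone does nothing, and about 10% for the misleading pair. Both depend on an assumed mentoring effect of 0.5 SD, correlation of 0.6, full follow-up and two-sided 5% level. Setting g = 0 is a stress case and not what the authors expect. The consequence is for interpretation and for the effect sizes passed to the definitive trial. Sample size and the validity of the model are not affected. The change should be made, as it needs no new data.

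**What to change.** From the same ANCOVA:

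1. Report Group 2 versus Group 1 (goal-setting alone) and Group 3 versus Group 1 (goal-setting plus mentoring) with 95% confidence intervals, beside Group 3 versus Group 2.
2. Keep the pooled contrast, but label it *goal-setting with or without mentoring* and reword its question to match.
3. Carry the arm-specific effect estimates with their intervals to the definitive trial, rather than the pooled estimate.

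The cost is a change of wording and two extra contrasts from a model already planned. The price in precision is that the standard error for goal-setting alone is about 15% larger than for the pooled contrast. At r = 0.6 and 25 per arm, the 95% interval for a pairwise contrast has a half-width of about 0.45 SD (1.99 × 0.226).

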#### *Physical fitness, health, and dietary assessment*

Health assessment covering medical history, anthropometric data, medication use, and blood pressure. A blood sample will be taken for lipid profile, to give a QRISK2 score [28]. This multifactorial score gives a percentage risk for cardiovascular disease over a 10-year period. The QRISK2 has been independently validated [29] and is based on data specific to the UK allowing for differing ethnicity and using postcodes to account for deprivation. The aim is to identify asymptomatic people without established cardiovascular disease (CVD) but who have a combination of risk factors which puts them at high total risk (estimated CVD risk ≥ 20% over 10 years) of developing atherosclerotic CVD for the first time. Blood samples will be analyzed by independent National Health Service laboratory staff. The blood results are copied to the participant’s primary care physician and also screened by [name]. Health needs (for example, regarding cardiovascular risk reduction) will be identified and details will be available to support the goal-setting interview process. If screening indicates a need for urgent medical attention in the view of the physician ([name]), an appropriate referral will be made.

Senior Fitness Test (SFT) [30]. Several brief subtests from the SFT will be used, involving common activities such as getting up from a chair, walking, lifting, bending, and stretching. These provide an assessment of upper and lower body strength, flexibility, and agility.

Physical fitness will be evaluated by determining predicted aerobic capacity from a submaximal graded exercise step test [31].

Mediterranean Diet Adherence Screener (MEDAS) [32]. This 14 item questionnaire examines participants’ adherence to a typical Mediterranean diet in terms of food intake habits and the frequency of consumption of foods such as olive oil and pulses. Adherence to this type of diet has been related to better physical and mental health outcomes [33].

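### QRISK2 cannot confirm a change in physical or cognitive activity: only the goal-setting arms get a risk-informed interview that can lead to medical care, and the score is aimed at people without CVD in a trial with no exclusions (minor)

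*Protocol article*

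**What the plan says.** All places are in the protocol article.

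- **Data analysis:** "QRISK2 scores will be compared to examine whether they provide confirmatory evidence of behavior change". The planned ANCOVA and its two contrasts (Group 1 against Groups 2 and 3 combined, and Group 2 against Group 3) are stated for cognitive and physical activity.
- **Physical fitness, health, and dietary assessment**, on the score: "This multifactorial score gives a percentage risk for cardiovascular disease over a 10-year period". On its purpose: "The aim is to identify asymptomatic people without established cardiovascular disease (CVD) but who have a combination of risk factors".
- **Participants:** people over 50 who attend the center "will be invited to participate, with no exclusions". The Abstract and the Intervention section nevertheless describe the participants as healthy.
- **Physical fitness, health, and dietary assessment**, on use of the findings: "Health needs (for example, regarding cardiovascular risk reduction) will be identified and details will be available to support the goal-setting interview process". Blood results also go to the primary care physician, and urgent referral is possible. Neither is limited to an arm.
- **Intervention:** the goal-setting interviewer can see the health risks found at baseline, and a GP consultation is one of the external routes by which a goal may be pursued. Group 3 has the same interview. Group 1 has a general talk about what the center offers.

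**The concern.** The primary outcomes, FCAS and PASE, are self-reported activity scales. A score built partly on blood results and blood pressure looks like an objective check on them, so a favorable QRISK2 difference is likely to be read as proof that activity changed. The article's own account gives two reasons for caution.

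First, the goal-setting arms have a route to a lower score that Group 1 is not described as having: identified risk, then interview, then GP, then treatment. This route needs no change in physical or cognitive activity.

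Second, the score is presented for people without established CVD, while nothing in the entry rules keeps people with CVD out.

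The trial is meant to guide the choice of measures for a definitive trial, so a misreading here would carry forward.

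**Working it through.** There is no stated QRISK2 effect, SD, power or CVD prevalence to reproduce. The one related figure agrees: 3 arms × 25 = 75. The main check sets the passages side by side.

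**Step 1: routes from baseline findings to a changed score**

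| Route | Group 1 | Groups 2 and 3 | Can it create a between-arm difference? |
|---|---|---|---|
| Blood results copied to the physician | yes | yes | Not by itself; it may dilute a contrast |
| Urgent referral after screening | yes | yes | Not by itself |
| Identified risks used in the goal-setting interview, with GP consultation as a possible follow-on | not described | yes | Yes |
| Activity changed through goal-setting | no goal-setting | yes | Yes |

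The last two rows act on the same comparison, Group 1 against Groups 2 and 3. A QRISK2 difference cannot tell them apart. Groups 2 and 3 share the same interview, so the third route mainly affects the first contrast.

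**Step 2: who is scored**

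The Participants section applies no health criterion. The QRISK2 text is aimed at people without established CVD. Calling the sample healthy does not bridge the two, because no rule secures it. Any participant with CVD at entry would lie outside the score's described purpose. How many there would be is unknown.

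**Step 3: cost of restricting the comparison (illustration only)**

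Assumptions: two-sided alpha 0.05, power 80%, no dropout, no gain from covariates, CVD share equal across arms, and the two activity contrasts also used for QRISK2. The CVD share is assumed, and a range is shown.

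With n per arm = 25 × (1 − share), the minimum detectable standardized difference is (1.960 + 0.842) × √(1/n₁ + 1/n₂).

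- Group 1 against Groups 2 and 3, share 0%: 2.802 × √(1/25 + 1/50) = 0.686
- Group 2 against Group 3, share 0%: 2.802 × √(2/25) = 0.792

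| Assumed CVD share | Remaining of 75 | Per arm | 1 vs 2+3 (SD) | 2 vs 3 (SD) |
|---|---|---|---|---|
| 0% | 75 | 25 | 0.686 | 0.792 |
| 10% | 67.5 | 22.5 | 0.723 | 0.835 |
| 20% | 60 | 20 | 0.767 | 0.886 |
| 30% | 52.5 | 17.5 | 0.820 | 0.947 |

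Even with everyone included, only large differences are detectable. Restriction makes this moderately worse and does not change the exploratory character of the comparison.

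**The case against.** The strongest reply is that the article asks an open question. It will look at whether QRISK2 supports behavior change, in a feasibility study that is partly about judging measures. QRISK2 is not primary, no decision rests on it, and fitness is also measured directly by the Senior Fitness Test and a step test. This stands, and it is why the point is minor.

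Behavior change here also covers diet and health, and seeing a GP about a health goal is something the intervention may intend. A score lowered that way is partly a genuine effect of randomized allocation, not contamination. This also stands. What survives is narrower: such a score would not isolate physical or cognitive activity, the domains of the primary outcomes.

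Some stronger readings are tempting but not supported:

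- **That invalid scores will be mixed into the comparison.** The open entry rule governs the trial, not each measure's analysis set. The article does not say that people with CVD will be scored or compared, and a fuller plan may settle this.
- **That sending results to the physician biases the arms.** The text concerns blood results, not the risk score, and does not limit the copying to any arm.
- **That fixed components distort the contrast.** The score is described as "allowing for differing ethnicity and using postcodes to account for deprivation". Such items do not respond to allocation; randomization balances them in expectation, so they are not a source of systematic between-arm difference.

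**Conclusion.** The concern holds in a limited form. On the article's own account, a lower QRISK2 in Groups 2 and 3 than in Group 1 could partly come from medical treatment prompted by the risk-informed interview, so it would not confirm a change in physical or cognitive activity. The score's described target population also does not match an entry rule without exclusions, and the article does not reconcile the two.

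Severity is minor. The size of any treatment contribution cannot be derived from the document, nor can the share of participants with CVD. The conclusion rests on two readings: that the comparison is between arms, and that the control discussion, as described, does not use the baseline risk findings. It does not depend on the assumed CVD shares, which only illustrate the cost of the fix.

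**What to change.** 1. Compare QRISK2 in participants with no CVD in the baseline medical history, by ANCOVA adjusting for baseline QRISK2 and gender (the stratification factor). The restriction uses pre-randomization information only, so it preserves the randomized comparison.
2. Show blood pressure and lipids separately beside the score.
3. Tabulate blood-pressure and lipid medication started after baseline, by arm and descriptively. Do not exclude those participants: starting medication happens after randomization and may be caused by the intervention, so exclusion could introduce selection bias.
4. Describe QRISK2 as exploratory, supportive information on cardiovascular risk, not as confirmation of behavior change.

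Cost: analysis and wording only. The health assessment, with medical history, medication, blood pressure and lipids, is listed among the measures taken at both baseline and 12 months. The downside is a somewhat smaller QRISK2 analysis set and the modest loss of precision shown in the illustration.
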